## Abstract

**Background:**

Anhedonia, including social, physical, and less-known, olfactory, stands as a core symptom of major depressive disorder (MDD). At the neurobiological level, anhedonia has been associated with abnormal activity within the reward system, suggesting a key role for dopamine. Repetitive Transcranial Magnetic Stimulation (rTMS) has emerged as an innovative treatment for alleviating depressive symptoms. Stimulation of the dorsolateral prefrontal cortex (DLPFC) has been shown to both improve anhedonia and induce dopamine release. Moreover, research suggests that the efficacy of rTMS is improved when applied to an activated brain network rather than at rest. Our goal is to induce a dual activation of the reward system using a combined rTMS protocol and an intervention based on pleasant odorant exposure known to stimulate this system.

**Methods:**

In this randomized controlled trial, we propose to combine rTMS targeting the left DLPFC with pleasant odorant stimulation to alleviate depressive symptoms. A total of 80 patients with treatment-resistant MDD will be randomly assigned to two groups and will receive 50 sessions of either: 1- rTMS and hedonic olfactory stimulations, or 2- rTMS alone. We will conduct pre- and post-assessments measuring depression severity, physical, social, and olfactory anhedonia, as well as the connectivity and activity of brain regions involved in the pathophysiology of depression and the reward circuitry.

**Discussion:**

This study may strengthen the development of more effective rTMS interventions and pave the way for the establishment of rTMS combined with olfactory training as a safe, effective, and easily accessible treatment for MDD patients. In addition, this study will contribute to a better understanding of the mechanisms and physiopathology of MDD.

**Trial registration number:**

#NCT05661383.

## 1 Introduction

### 1.1 Background and rationale

#### 1.1.1 Major depressive disorder and anhedonia

Major depressive disorder (MDD) stands as the most common psychiatric disorder, affecting 4.4% of the world's population (World Health Organization, 2017). Among the clinical manifestations, anhedonia, the inability to experience pleasure, is one of the core symptoms of depression, affecting 70% of patients with MDD and linked to increased suicide risk. Furthermore, it is typically resistant to the first-line treatment (Kelly et al., 2022), making it one of the priorities of mental health research (Ducasse et al., 2021). This symptom appears to be rooted in a dysfunction of the reward system, i.e., hyperactivity in the prefrontal cortex (PFC) and hypoactivity in the ventral striatum (Gorwood, 2008), in which dopamine (DA) plays a key role. Furthermore, the symptom of motivational anhedonia has been linked to an abnormal availability of DA receptors in the ventral striatum (Peciña et al., 2017). Importantly, anhedonia can be physical and social, but it can also affect the senses, including olfaction.

Olfactory anhedonia has been shown to contribute to disrupted eating, social interactions, and mood (Clepce et al., 2010). Interestingly, the reward system, impaired in anhedonia, is closely connected to the olfactory system through the olfactory tubercle located in the ventral striatum, directly linked to the ventral tegmental area (Ikemoto, 2007). Olfactory stimulation has even been shown to activate DA neurons within the reward circuits in mice (Midroit et al., 2021) and brain regions of the mesocorticolimbic pathway in humans (Rolls et al., 2003).

Furthermore, several studies have shown that odors can improve mood and feeling of calm (Canbeyli, 2022), and that improved olfactory capabilities are associated with a reduction in depressive symptoms (Sabiniewicz et al., 2022) in participants without psychiatric disorders. While these findings are encouraging, the impact of such olfactory interventions in patients with MDD remains unclear.

#### 1.1.2 Repetitive transcranial magnetic stimulation protocol in MDD

Over the past decades, repetitive transcranial magnetic stimulation (rTMS) has emerged as an effective treatment for treatment-resistant symptoms in patients with MDD. This non-invasive brain stimulation technique modulates the activity and connectivity of a targeted brain network by applying a magnetic coil over the scalp. The effect depends on the stimulation parameters and the underlying brain network activity. It can result in either an increase or a decrease in the activity of the targeted network. Based on neuroimaging studies showing an imbalance in activity between the right and left dorsolateral prefrontal cortex (DLPFC) in patients with MDD (George et al., 1994; Grimm et al., 2008), it has been proposed to use either high-frequency rTMS over the left DLPFC or low-frequency rTMS over the right DLPFC to alleviate depressive symptoms. Although recent evidence-based guidelines report beneficial effects of rTMS on depressive symptoms (Lefaucheur et al., 2020), only 30% of patients achieved remission (Vida et al., 2023), leaving much room for optimization of rTMS protocols.

#### 1.1.3 Optimize rTMS protocol

A better knowledge of the underlying mechanisms of rTMS should help to optimize the clinical application of rTMS in depression. Several neuroimaging studies have shown that stimulating the left DLPFC leads to DA release in the ventral striatum in healthy participants (Strafella et al., 2001; Fonteneau et al., 2018), as well as in patients with MDD (Pogarell et al., 2006, 2007), and schizophrenia (Brunelin et al., 2011). These findings suggest that modulation of subcortical DA transmission may be a key mechanism underlying the therapeutic effects of rTMS.

Furthermore, the combination of rTMS with additional therapeutic strategies, including psychotherapy (Donse et al., 2018), cognitive behavioral therapy (Vedeniapin et al., 2010), and pharmacological treatments (Liu et al., 2014; but see Brunelin et al., 2014 for contradictory results), has been demonstrated to enhance the clinical efficacy of rTMS in depression. The same synergistic effect has also been observed with exposure therapy in individuals with tobacco use disorder (Dinur-Klein et al., 2014) and in patients with post-traumatic stress disorder (Isserles et al., 2013). These synergistic effects are thought to be due to the initial state of the neural network activation, that influences the effects of non-invasive brain stimulation (NIBS), with stimulation of an already activated network being more effective and enhancing the effects of the stimulation (Silvanto and Pascual-Leone, 2008).

Altogether, one may hypothesize that the dual-activation of the DA reward system with both TMS over the DLPFC and olfactory-based intervention with pleasant odorant inducing DA release may be particularly relevant in the treatment of anhedonia (Neige et al., 2024).

#### 1.1.4 Aim and hypotheses

This study aims to electrochemically stimulate the DA reward circuitry to alleviate anhedonia and achieve remission in patients with treatment-resistant MDD. We therefore propose to increase DA release from ventral tegmental area neurons and thereby increase ventral striatal activity, which is reduced in anhedonia. For this purpose, we will combine rTMS applied over the left DLPFC with hedonic olfactory stimulation (i.e., odorants with pleasant hedonic value), both known to modulate the DA reward system.

- By stimulating the DLPFC with rTMS, we aim to enhance its feedback control over subcortical structures.- By using odorants with positive hedonic value known to recruit/activate the reward circuit, we aim to enhance DA release and thereby increase ventral striatal activity which is reduced in anhedonia,

Based on evidence linking anhedonia to reduced DA transmission and blunted mesocorticolimbic network functional connectivity (Phillips et al., 2023), we hypothesize that rTMS would alleviate depressive symptoms through changes in functional and effective connectivity within DA-related brain regions.

We propose that the combined approach may be more effective in enhancing DA release, as both methods stimulate DA activity, resulting in greater improvements in anhedonia and a more pronounced reduction in depressive symptoms compared to rTMS alone.

### 1.2 Objectives

#### 1.2.1 Primary objective

The main objective is to investigate the acute clinical effect of the combination of rTMS and hedonic olfactory stimulation on depressive symptoms compared to rTMS alone, measured as the number of patients who achieved remission after the treatment (number of patients with a MADRS_10_ < 10).

#### 1.2.2 Secondary objectives

##### 1.2.2.1 Clinical outcomes

We will assess the acute and long-term effects of the treatment on several clinical features of MDD: remission (MADRS_10_ < 10) and response (reduction of at least 50% in MADRS_10_ score), severity of self-rated depression (BDI_13_), physical and social anhedonia and apathy immediately after the treatment, after 1-month and 3-month follow-up.

##### 1.2.2.2 Behavioral outcome

We will investigate the effect of the treatment on cognitive biases using a free viewing task (see 4.2.2.1 Eye tracking free-viewing task), at baseline, after 1, 5, and the 50 sessions of rTMS.

##### 1.2.2.3 Brain connectivity and activity assessments

We will explore the effects of the treatment on brain connectivity and activity within the brain regions involved in the reward and olfactory processes. Additionally, we will also investigate the relationship between brain changes and clinical features changes.

##### 1.2.2.4 Olfactory anhedonia

Finally, our last objective will be to better characterize olfactory anhedonia (i.e., the impaired olfactory perception of pleasant odorants) by investigating its association with physical and social anhedonia, but also with early trauma. Olfactory anhedonia will be assessed before, immediately after treatment, after 1-month and 3-month follow-up through specific testing.

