#### 2.4.4 Olfactory anhedonia

Olfactory anhedonia will be assessed using an olfactory test in which the hedonic value of odorants will be evaluated before and after the treatment, as well as at 1 and 3 months after the treatment, and compared between the two groups. The relationship between olfactory anhedonia and physical and social anhedonia will be investigated, as well as its association with early life adversity.

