	**Study period**						
	**Patients with MDD**						**Healthy volunteers**
	**Inclusion**	**Allocation**	**Post-Allocation**		**Follow-up**		**Experimentation**
**Timepoint (week)**	**-1**	**0**	**1**	**2**	**6**	**14**	**1**

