**Assessments:**							
MADRS	**X**	**X**		**X**	**X**	**X**	
BDI		**X**		**X**	**X**	**X**	**X**
CTQ		**X**					**X**
Chapman scales		**X**		**X**	**X**	**X**	
SHAPS		**X**		**X**	**X**	**X**	**X**
AES		**X**		**X**			**X**
ETOC/hedonic perception		**X**					**X**
FVT		**X**		**X**			
MRI		**X**		**X**			
Dual-site TMS		**X**		**X**			**X**

iTBS, intermittent Theta Burst Stimulation; MDD, Major Depressive Disorder; MADRS, Montgomery and Asberg Depressive Rating Scale; BDI, Beck Depression Inventory; CTQ, Childhood Trauma Questionnaire; SHAPS, Snaith-Hamilton Pleasure Scale; AES, Apathy Evaluation Scale; ETOC, European Test of Olfactory Capabilities; FVT, Free-Viewing Task; MRI, Magnetic Resonance Imagery; TMS, Transcranial Magnetic Stimulation.

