##### 4.4.1.2 Clinical data analysis

The proportion of remissions and responses will be investigated using chi-squared tests or Fisher's exact test. Changes in scores of depression severity, anhedonia and olfactory capabilities over the study period within the two groups will be analyzed using a mixed 2-way repeated measures ANOVA (GROUP^*^TIME) or a generalized linear mixed model depending on the distribution of the data. Pearson correlations will be performed to examine the relationship between olfactory anhedonia and pre-treatment physical and social anhedonia, as well as the relationship between childhood trauma severity and response to treatment, the relationship between childhood trauma severity and anhedonia (physical, social, and olfactory), and the relationship between childhood trauma severity and depression severity. Type of medication and type of depression (unipolar vs. bipolar) will be included in the analysis. We did not expect differences in response between patients with unipolar and bipolar depression.

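### Olfactory anhedonia is to be compared between arms after treatment and at 1 and 3 months, but Table 1 schedules the odour tests for patients only once, at week 0

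*Protocol article*

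**What the plan says.** The text of the protocol article is consistent about when olfactory anhedonia is measured.

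- The abstract (Methods) announces "pre- and post-assessments measuring depression severity, physical, social, and olfactory anhedonia".
- Section 1.2.2.4 says: "Olfactory anhedonia will be assessed before, immediately after treatment, after 1-month and 3-month follow-up through specific testing".
- Section 2.4.4 has the odour ratings "evaluated before and after the treatment, as well as at 1 and 3 months after the treatment, and compared between the two groups".
- Section 4.4.1.2 plans a two-way mixed ANOVA (group by time), or a generalized linear mixed model, for "Changes in scores of depression severity, anhedonia and olfactory capabilities over the study period within the two groups".

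The instrument for olfactory anhedonia is the 20-odorant hedonic judgment test (section 4.2.1.6). Olfactory capabilities is the heading used for the ETOC (section 4.2.1.5).

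The visit schedule (section 2.5, Table 1) puts both instruments in a single row, "ETOC/hedonic perception". For patients that row has one mark, at week 0. It has another mark for the single healthy-volunteer visit. No other row of the table carries an odour rating.

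**The concern.** The table is what visit staff are likely to work from, and it provides no odour rating after treatment starts. Olfactory anhedonia is the symptom closest to the component that distinguishes the two arms, so its change under treatment is among the more informative secondary results the trial could give. If the schedule is followed as printed, that result does not exist. A rating not taken at week 2, 6 or 14 cannot be obtained later.

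The single baseline mark is also not an obvious slip. Each instrument has a use that needs only one administration: the hedonic test selects each patient's odorants (section 2.3), and the ETOC excludes anosmia (section 2.2.1). Staff reading Table 1 would have no reason to suspect that a repeat was intended.

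**Working it through.** The plan gives no figure for this point, so the check is a comparison of text and table, followed by a count.

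**1. Visits by source (patients).** Table 1 has patient columns for weeks -1, 0, 1, 2, 6 and 14. Treatment lasts two weeks, so week 2 is the end of treatment, and weeks 6 and 14 are the 1-month and 3-month follow-ups.

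| Source | Week 0 | Week 2 | Week 6 | Week 14 |
|---|---|---|---|---|
| Sections 1.2.2.4 and 2.4.4, hedonic test | yes | yes | yes | yes |
| Abstract, olfactory anhedonia | yes | yes | not stated | not stated |
| Table 1, ETOC and hedonic row | marked | blank | blank | blank |
| Table 1, Chapman scales | marked | marked | marked | marked |
| Table 1, SHAPS | marked | marked | marked | marked |

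The blanks do not look like a fault of text extraction. In the odour row the week 0 mark is followed by four empty cells (weeks 1, 2, 6, 14) and then the healthy-volunteer mark, which matches the header. The MADRS, BDI, Chapman and SHAPS rows keep their marks at weeks 2, 6 and 14.

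**2. Count.** Time points per patient are 4 in the text and 1 in the table, so 3 are missing.

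- With all 80 patients retained: 3 × 80 = 240 unscheduled ratings.
- With the protocol's 7% attrition (80 × 0.93 = 74.4, about 74 patients), and assuming those lost miss all three visits: 3 × 74 = 222.
- If the trial stopped with the 40 patients of the interim analysis: 3 × 40 = 120.

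**3. Consequence for the planned model.** With 2 groups and k time points, the group-by-time term has (2 − 1)(k − 1) degrees of freedom.

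- Text, k = 4: 1 × 3 = 3.
- Table 1, k = 1: 1 × 0 = 0.

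With k = 1 there is no change score and no interaction to estimate. The only contrast left between arms is at baseline, before any treatment.

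**4. Imputation does not help.** Section 4.4.2 uses LOCF and requires a pre-treatment and at least one post-treatment evaluation. Applied to this outcome, that rule leaves no patient in the analysis. If a post-treatment evaluation on another scale is taken to satisfy the rule, LOCF carries the baseline rating forward and every change is exactly 0 in both arms.

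**5. ETOC.** No section names a follow-up visit for the ETOC. The conflict arises because section 4.4.1.2 models change in olfactory capabilities, which needs at least 2 time points, while Table 1 gives 1.

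**The case against.** The best answer is that the text is explicit, agrees with itself, and should be taken as governing. Table 1 is introduced as an overview and is incomplete elsewhere: the free-viewing task after 1 and 5 sessions is not marked, the YMRS has no row, and apathy is unmarked at weeks 6 and 14 although section 1.2.2.1 includes it at follow-up. On that reading the blanks are a clerical omission and the data will be collected. This may well be so, but the document does not say which source governs. Section 7.3 calls the manuscript the full protocol, so no fuller document can be assumed to settle it. A schedule with several gaps is a reason to correct it, not to rely on staff reading past it.

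Four narrower objections are fair:

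- The loss is partial. Section 1.2.2.4 aims mainly at associations with physical and social anhedonia and early trauma. The Chapman scales, CTQ and hedonic test are all marked at week 0, so these survive. The between-arm comparison comes from section 2.4.4.
- The count of 240 is a ceiling.
- The ETOC conflict is weaker than that for the hedonic test, because it rests on one term in the analysis section and a single baseline ETOC suits its eligibility role.
- This is the last-listed secondary objective. The primary outcome, sample size and interim boundary are untouched.

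These points limit the size of the problem. They do not remove the contradiction.

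**Conclusion.** The concern holds. The text requires four hedonic assessments per patient and a comparison of the arms, while the visit schedule provides one, before treatment. If Table 1 is followed, the longitudinal and between-arm part of the olfactory anhedonia objective cannot be estimated, and up to 240 ratings (about 222 at the protocol's attrition rate) are never scheduled. The same gap would appear at the interim analysis, which repeats the secondary analyses (section 5.1.2). For the ETOC, the planned change analysis has no second time point under any statement in the document.

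The conclusion is conditional on staff working from Table 1. If they follow sections 1.2.2.4 and 2.4.4, the hedonic data will exist and the fault is confined to the table. It should be corrected in either case, because the loss is permanent for each patient who passes those visits untested.

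**What to change.** 1. Split the Table 1 row in two. Mark the hedonic judgment test for patients at weeks 0, 2, 6 and 14, in agreement with sections 1.2.2.4 and 2.4.4.
2. For the ETOC, either mark the post-treatment visits at which olfactory capabilities will be modelled, or remove olfactory capabilities from the change analysis in section 4.4.1.2 and keep the ETOC as a baseline test.
3. If the table describes what is really done, withdraw the longitudinal olfactory objective instead: limit sections 1.2.2.4, 2.4.4 and 4.4.1.2 and the abstract to the baseline associations. This is the less attractive option, since it gives up a stated outcome.

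The cost of the first option is a correction to one table and a 20-odorant rating at three visits that patients already attend, with somewhat longer visits. A repeat ETOC would add further time, which is a reason to choose deliberately under point 2.

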### 1.3 Trial design

This is a prospective, randomized, double-blind, and parallel-group controlled trial. The study aims to compare the clinical benefits of two interventions: rTMS alone and rTMS combined with olfactory stimulation.

## 2 Methods: participants, intervention, and outcomes

### 2.1 Study setting

This trial is a single-center study. All the patients will be recruited at Centre Hospitalier Le Vinatier (Lyon, France). Healthy volunteers, matched for sex and age, will also be recruited to compare several clinical and biological features at baseline. All measurements and interventions will be performed at the same site, to ensure a uniform and controlled study environment.

### 2.2 Eligibility criteria

#### 2.2.1 Patients with MDD

To be eligible for the study, patients must meet the following criteria: be 18 years or older, have a primary diagnosis of single or recurrent non-psychotic major depressive disorder (unipolar or bipolar) episode according to the Diagnostic and Statistical Manual of Mental Disorders, fifth edition (DSM-5) criteria, scored 20 or more on the 10-item Montgomery and Asberg Depressive Rating Scale (MADRS) (Montgomery and Åsberg, 1979) and scored higher than 2 on the MADRS anhedonia score (item #8). All patients should be able to speak and read French, and sign a written informed consent.

Patients with unipolar depression should be on stable antidepressant medication for at least 4 weeks prior to inclusion with no mood changes (after at least one previous treatment failure). Patients recruited for this study had a treatment-resistant depressive episode, defined as failure to respond to at least two antidepressant regimens despite adequate dosage, duration and adherence to treatment (McIntyre et al., 2023). Patients will remain on the same stable antidepressant medication throughout the trial without any changes. Benzodiazepines are not allowed.

Patients with bipolar depression should have treatment-resistant bipolar depression at enrolment, despite optimized mood-stabilizing treatment of adequate duration and dosage (for at least one month). Throughout the study period, patients will be on stable mono- or bi- therapy with mood stabilizers, without antidepressants or benzodiazepines (Bulteau et al., 2019).

Augmentation strategy with antipsychotics is allowed.

Participants will be not eligible if they have: anosmia [as verified by the European Test of Olfactory Capabilities (ETOC) (Thomas-Danguin et al., 2003)], whether congenital, or due to upper respiratory tract infection, nasal and/or sinus disease, brain injury or nasal surgery; neurological disorders; concurrent comorbid psychiatric disorders or substance abuse (except tobacco); contraindications to TMS (implanted medical devices or metallic foreign body in the head); contraindications to MRI; history of non-response to treatments based on sensory stimulation or rTMS; pregnant or breastfeeding mothers (controlled by urine pregnancy tests); a conservatorship or guardianship order.

Patients will be free to withdraw from the study without having to justify their decision. The principal investigator may end the patient's participation due to loss to follow-up, severe intercurrent pathology, modification/discontinuation of treatment, or change of diagnosis.

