### 2.3 Intervention

All stimulations for therapeutic intervention will be delivered using a MagPro X100 (MagVenture, Mag2Health, France) equipped with a 65 mm figure-of-eight coil with active cooling (MCF-Cool B65). Patients will be comfortably installed in a dedicated room for brain stimulation. During each session, the 3D T1-weighted images of all participants will be used for neuronavigation and the position and orientation of the coil will be monitored using a neuronavigation system (Syneika system, France).

At the first session, the primary motor cortex (M1) hand area will be located by identifying the optimal scalp sit (hotspot) that elicits the largest amplitude of motor evoked potentials (MEPs) in the right hand's first dorsal interosseus (FDI) muscle for a given intensity. The resting motor threshold (rMT) will then be established as the lowest stimulation intensity to evoke at least 5 MEP of 50 μV peak-to-peak amplitude from 10 consecutive (Rossini et al., 1994).

For the rTMS protocol, the coil will be positioned over the left DLPFC based on the individual anatomical T1-weighted MRI. The targeted left DLPFC will be identified based on a predefined identification by the Syneika neuronavigation system, i.e., the junction between areas BA9 and BA46, according to the algorithm proposed by Mylius et al. (2013). The exact same target will be maintained for each rTMS session to ensure precise and reproducible placement of the stimulation coil.

The rTMS protocol includes 50 sessions over 10 days (i.e., 5 sessions per working day, 1 h apart, for 2 weeks). Each session lasts 9min40 and involves 1,800 pulses at 90% rMT, delivered in bursts of 3 pulses at 50 Hz, repeated at 200 ms intervals for 2 s (i.e., at 5 Hz). This particular rTMS protocol is called intermittent theta-burst stimulation (iTBS). A 2-second train of iTBS is repeated every 10 s (Cole et al., 2022).

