### 2.6 Sample size

#### 2.6.1 Patients with MDD

The sample size was estimated using EasyMed online software (https://easymedstat.fr), with an a priori power analysis based on a comparison of two binomial proportions (approximation of arscin).

We expect an approximately twofold increase in the remission rate for the iTBS combined with olfactory training group, compared to the iTBS alone group. This expectation is based on results from similar protocols using dual activation of the same neural network, such as the combination of high-frequency rTMS and visual smoking cues in individuals with tobacco use disorder, which reported 1.8-fold higher remission rate in the combination group than in the rTMS group alone (Dinur-Klein et al., 2014), and deep TMS with exposure in patients with post-traumatic stress disorder (Isserles et al., 2013), which reported a 3.5-fold higher response rate in the combination group than in the rTMS alone group.

Based on previous studies investigating the clinical efficacy of rTMS in treatment-resistant depression in both RCTs (Vida et al., 2023) and naturalistic settings (Bouaziz et al., 2023), we predict an approximate remission rate of 30% for the iTBS alone group. Thus, the expected remission rate for the iTBS combined with olfactory training group is estimated to be 60%. With a chi-squared test, an α risk of 5%, and a ß-power of 80%, a total of 74 MDD patients (37 per group) are required to be included.

As all patients enrolled in this trial will receive active treatment, we anticipate a low attrition rate (7%) and therefore plan to recruit a total of 80 patients with MDD (40 per group).

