#### 4.4.2 Withdrawals and missing data

All participants will be included in an intention-to-treat (ITT) analysis, based on their initial group assignment, even if they withdraw or fail to complete the study. For withdrawn participants, their data will still be analyzed as if they completed the study, and missing data will be imputed using the Last Observation Carried Forward (LOCF) method. Only patients with a pre-treatment evaluation and at least one post-treatment evaluation will be included in the analysis.

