### 6.6 Ancillary and post-trial care

Patients will remain under double-blind throughout the follow-up period with no change in treatment. Follow-up will be carried out for a period of 3 months. After inclusion, patients may not participate in any other clinical research will be permitted during the study.

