### 7.3 Plans to give access to the full protocol, participant level-data and statistical code

This manuscript is the full protocol of the study. Anonymized dataset and statistical code may be shared with other scientists upon reasonable request.

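### Patients whose treatment changes can be taken out of the trial, and LOCF then replaces 1- and 3-month ratings that could still have been obtained

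*Protocol article*

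**What the plan says.** All references are to the protocol article.

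- **Exit rule.** The withdrawal paragraph of Section 2.2.1 reads: "The principal investigator may end the patient's participation due to loss to follow-up, severe intercurrent pathology, modification/discontinuation of treatment, or change of diagnosis".
- **No treatment change allowed.** Section 2.2.1 also requires antidepressant medication to stay the same for the whole trial. Section 6.6 extends this to follow-up: "Patients will remain under double-blind throughout the follow-up period with no change in treatment".
- **Length of the iTBS course.** Section 2.3: "The rTMS protocol includes 50 sessions over 10 days". The course is therefore over by week 2.
- **Scheduled ratings.** Table 1 places the MADRS, BDI, Chapman scales and SHAPS at weeks 2, 6 and 14. Sections 1.2.2.1 and 2.4.2 make outcomes at 1 and 3 months secondary comparisons between the arms.
- **Analysis of leavers.** Section 4.4.2 announces an intention-to-treat analysis of all participants by assigned group. On those who leave, it says: "For withdrawn participants, their data will still be analyzed as if they completed the study". The method it names for filling the gaps is single imputation: "missing data will be imputed using the Last Observation Carried Forward (LOCF) method". It then restricts the set: "Only patients with a pre-treatment evaluation and at least one post-treatment evaluation will be included in the analysis".
- **Retention.** Section 4.2.4.1 offers a visit schedule, reminders and payment according to visits attended. It does not mention visits after treatment is stopped or participation is ended.
- **Status of the text.** Section 7.3: "This manuscript is the full protocol of the study".

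**The concern.** Loss to follow-up makes a score unobtainable. A change of treatment does not: the patient can usually still come in and be rated. The exit rule handles the two alike, and the missing-data rule then replaces the rating that was not taken with an older one.

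Treatment changes in treatment-resistant depression are likely to depend on how the patient is doing. The ratings lost this way would therefore be lost in relation to outcome, and possibly at different rates in the two arms. The 1- and 3-month comparisons of remission, response, self-rated depression and anhedonia would then rest partly on carried-forward values where real ones could have been had. The primary week-2 comparison is exposed only through patients removed before that rating, whom Section 4.4.2 leaves out despite its intention-to-treat statement. Ratings that were never taken cannot be recovered by any later analysis plan.

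**Working it through.** **Step 1: how the rules combine.** The word *treatment* in the exit rule has two possible meanings.

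- (a) It includes medication. This fits the bans on change in Sections 2.2.1 and 6.6. A patient whose medication is altered between weeks 2 and 14 may be ended. If this happens before the next rating, LOCF supplies the week-6 and/or week-14 score. A relapse already rated at week 6 is carried forward correctly as a relapse, so the problem is a change and exit before the next rating.
- (b) It means only the iTBS course. The rule then reaches only patients who stop iTBS early.

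On either reading, a patient ended before the week-2 rating has no post-treatment evaluation and is excluded from the primary analysis.

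**Step 2: figures from the document (Section 2.6.1).** There are 40 patients per arm, with expected remission of 30% (iTBS alone) and 60% (combined) and attrition of 7%. The allowance reproduces: 74/0.93 = 79.6, rounded up to 80. Planned attrition from all causes is 0.07 × 80 = 5.6 patients. One wrong status moves an arm's remission rate by 1/40 = 2.5 points.

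Everything below is illustration. Relapse, exit and late-remission rates are assumptions, because the document gives none.

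**Step 3: relapse after week-2 remission, same rates in both arms.** Let p be week-2 remission, r the share of remitters relapsed by week 14, and e the share of relapsers ended before the relapse is rated. Assume no late remission. LOCF remission minus observed remission is p·r·e in each arm. The shift in the difference is (0.60 − 0.30)·r·e = 0.30·r·e. The number of patients involved is (24 + 12)·r·e = 36·r·e.

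| r | e | Observed difference (points) | LOCF difference (points) | Shift | Patients |
|---|---|---|---|---|---|
| 0.2 | 0.10 | 24.0 | 24.6 | +0.6 | 0.72 |
| 0.2 | 0.25 | 24.0 | 25.5 | +1.5 | 1.8 |
| 0.2 | 0.50 | 24.0 | 27.0 | +3.0 | 3.6 |
| 0.4 | 0.10 | 18.0 | 19.2 | +1.2 | 1.44 |
| 0.4 | 0.25 | 18.0 | 21.0 | +3.0 | 3.6 |

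The pair r = 0.4, e = 0.5 would need 7.2 patients, above the planned 5.6, and is left out. Setting 36·r·e = 5.6 gives r·e = 0.156 and a ceiling of 0.30 × 0.156 = 4.7 points. This ceiling applies only with equal rates.

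**Step 4: exits in one arm only.** Shift = 0.60·r·e_c − 0.30·r·e_a, with subscript c for combined and a for alone, and r = 0.4.

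- e_a = 0.25, e_c = 0: −0.30 × 0.4 × 0.25 = −3.0 points (1.2 patients).
- e_a = 0, e_c = 0.25: +0.60 × 0.4 × 0.25 = +6.0 points (2.4 patients).

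**Step 5: late remission after exit.** Let c be the share of week-2 non-remitters ended and m the share of those who later remit. Shift = 0.70·c_a·m − 0.40·c_c·m, with m from 0.2 to 0.4.

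- c = 0.1 in both arms (2.8 + 1.6 = 4.4 patients): +0.6 to +1.2 points.
- c = 0.1 in the combined arm only: −0.8 to −1.6 points.
- c = 0.1 in the iTBS-alone arm only: +1.4 to +2.8 points.

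The sign changes with the scenario, so the document fixes neither direction nor size.

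**The case against.** The other side has real points.

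- **The clause is permissive and one word is ambiguous.** The investigator *may* end participation and need not. Section 4.4.2 imputes only what is missing, so any score obtained would be used. Under reading (b), little of the LOCF problem at weeks 6 and 14 remains. This stands as a limit on the claim, which is that obtainable scores *can* be replaced. It does not remove the gap: discretion without criteria lets similar patients be handled differently, and nothing says the ratings continue.
- **The relapse model may overstate the shift.** It counts every relapser who was ended as a non-remitter at week 14, yet the new treatment may have restored remission, in which case LOCF is right. This stands.
- **The 7% is weak ground for a week-14 ceiling.** It was set for a sample size based on the end-of-treatment outcome and covers all causes of loss. This stands; the 4.7-point ceiling is only a rough guide.
- **The effect is small.** At 24% against 48% with 40 per arm, the standard error is √(0.24 × 0.76/40 + 0.48 × 0.52/40) = 10.4 points. Equal-rate shifts of 0.6 to 3.0 points are about 0.06 to 0.3 standard errors, on secondary outcomes. This stands and keeps the point from being a major one.
- **Follow-up on unchanged treatment is a different question.** Scores after a medication change would not answer it. This does not carry: Section 4.4.2 commits to intention to treat, and LOCF does not recover scores under unchanged treatment either.

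**Conclusion.** The concern holds. The exit rule and the missing-data rule together allow obtainable week-6 and week-14 ratings to be replaced by older ones, and allow early leavers to drop out of the primary analysis. No section keeps the ratings going.

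Direction and size are unknown. They depend on which arm changes treatment more, on relapse and on late remission. Under the assumed rates shown, the 3-month remission difference shifts by anything from −3.0 to +6.0 points. The secondary follow-up comparisons are mainly affected, and those chiefly if *treatment* includes medication. The change is worth making because it is cheap and prevents outcome-related missing data. It is not a threat to the primary result beyond patients ended before week 2.

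**What to change.** Amend the withdrawal paragraph of Section 2.2.1 so that stopping iTBS or changing medication is recorded (date, type, reason) but does not end participation. Take the ratings Table 1 already schedules at weeks 2, 6 and 14, including week 2 for those who stop iTBS early, unless consent is withdrawn or contact is lost. Analyse the observed scores by randomised group. Add a supportive analysis that counts a treatment change as non-remission. This takes no position on whether treatment should be changed, and leaves truly missing scores to Section 4.4.2.

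**Cost.** A protocol amendment with ethics review and one CRF field. Each affected patient adds up to two ratings after week 2 with the matching visit payments: at planned attrition, at most 5.6 × 2 = about 11 visits. Patients who stop iTBS early also need the week-2 rating. These visits are already planned for all 80 patients, and payment already follows attendance. If patients are already enrolled, they may need to be informed or re-consented, and the data would be collected under two rules.

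**Downside.** Some follow-up scores will reflect other treatment, which the supportive analysis can show.
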